## Methods and Analysis

### Overview and Structure of the Active Rehab Study

The Active Rehab Study Consortium was initially proposed in 2014 through an international meeting that included representation from the scientific community and sporting organizations. The core idea of a multi-sport, multi-age, and multi-country study evaluating treatment and management of concussion was refined into a formal protocol over a period of months by an executive research consortium. They titled this project “Role of Active Rehabilitation in Concussion Management: A Randomized Controlled Trial (The Active Rehab Study).” The final consortium, led by The University of North Carolina at Chapel Hill and Medical College of Wisconsin, includes collaborators and sites from the Canadian Football League (CFL, 9 team sites), New Zealand Super Rugby (NZR, 5 team sites), North American Colleges/Universities (6 school sites), and Wisconsin and North Carolina High Schools (8 school sites). Sports represented in the study include collision, contact, and non-contact sports for both males and females. Should professional cohort sample size not approximate anticipated numbers, an additional professional ice-hockey cohort may be included. The study is conducted in compliance with US and international guidelines for research under the primary protocol approval from The University of North Carolina at Chapel Hill Institutional Review Board. All participants provide written and informed consent prior to participation. Informed consent documentation is verified via an informed consent tracking form in the study data collection system and through communication with study cohort leads and sites throughout the course of the study.

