### Allocation to Study Arm

The two treatment arms (multidimensional active rehab and EGE progression) are assigned at random to the 28 sites in the study. Site level (cluster) randomization is utilized because the study team considered that patient-level randomization at a site would be prone to contamination between arms. Thus, all athletes at a given site receive the same protocol. All study sites are randomized to either the MDR (early rehabilitation) or the EGE [current return to sport strategy (16)]. To ensure a balanced of treatment arms across cohort, site randomization is stratified by (i.e., conducted within) cohort (NZR, CFL, College, HS). Colleges/universities and high school sites are stratified by size of school prior to randomization; CFL and NZR sites are not stratified. Due to the nature of the early and active treatment delineation, no allocation concealment such as masking or blinding is possible. The clinicians (site personnel) at the sites know their allocated arm. However, participants are not explicitly told about the role of their respective study arm. Site personnel at the MDR sites are trained to deliver the treatment separately from the site personnel at the EGE sites.

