### Participants and Eligibility Criteria

The inclusion criteria for participants in the trial are individuals rostered as an athlete at the study sites who consent to the study. Written, informed consent is administered during a pre-season baseline assessment. Target participant enrollment across all settings is estimated to be 3,500 at baseline and 100–200 in each study arm (total *n* = 200–400) post-injury. The post-injury protocol includes all consented athletes with a SRC at each site and meeting the following criteria.

Our current trial aligns with common elements from the NCAA-DOD Grand Alliance Concussion Assessment, Research, and Education (CARE) Consortium (15). As such, we have defined SRC in accordance with the Department of Defense (DoD) operational definition as *a change in brain function following a force to the head, which may (or may not) be accompanied by temporary loss of consciousness (if LOC, temporary is defined as* <*30 min based on the Mayo TBI severity guidelines), but is identified in awake individuals with measures of neurologic and cognitive dysfunction, as indicated by 1 or more of the 22 symptoms from the Sport Concussion Assessment Tool (SCAT) symptom checklist* (16). No athlete with a Glasgow Coma Scale <13 enters the treatment progression of either arm.

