As is standard with SRC studies (15), identifying the SRC is determined by medical professionals at each site involving a physician and other team-based healthcare provider (based on clinical exam and their interpretation of objective findings inclusive of the definition above). If medically diagnosed with a SRC, and no other indicators of more moderate to severe TBI as defined in the Mayo definition above (17), consented participants are eligible for enrollment in the treatment protocol. Documentation of the clinical diagnosis and identification of the medical personnel making the diagnosis are recorded in study case report forms. For inclusion in the post-injury protocols, the SRC must occur in a rostered sport for a high school or collegiate sport at their school or for their specific rostered sport (and team sanctioned activity) for the professional cohort. Individuals with any positive/abnormal clinical neuroimaging finding(s) following injury are not entered into the post-injury protocol or are discontinued from their arm treatment protocol if these findings are observed after the protocol has been initiated. Although these individuals are discontinued from the treatment protocol, we continue to collect assessment time point data on these individuals and documentation for their overall care.

We anticipate ~10–15% attrition due to study demands and seasonal nature of sport through full clearance to return to sport. However, we expect 20–30% attrition for the 1-month timepoint due to this timing and other potential participant follow-up issues. The study protocol incorporates contacting participants to keep them engaged.

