***Specific Aim 1***
*(evaluation of effectiveness):* For analyses of our primary endpoints, Cox proportional hazards regression models (35) will be used to compare time to return to play and time to asymptomatic between the EGE and MDR groups. The specific outcomes for the Cox models will be time from date of injury to: (1) date of medical clearance for full return to participation and (2) asymptomatic date. The Wei-Lin robust variance estimator will be used to account for the effect of cluster-randomization by site (36).

For our secondary endpoints (clinical and quality of life measures), recovery trajectories will be examined by use of General Linear Mixed regression models and non-parametric smoothers. Random effects will be utilized to account for the effect of clustering by site and the effect of repeated observations over time within an individual participant. The time axis to be modeled in both sets of analyses is time from initiation of the treatment (defined as stable symptoms for 24 h), and time will be treated as a continuous variable in all analyses.

We will also assess potential predictors of attrition (e.g., gender, race, socioeconomic status). If no predictable patterns are observed for missing data (i.e., missingness occurs at random), no imputations will be conducted. Inverse probability of attrition weights based on the factors influencing attrition will be used to account for potential selection bias due to attrition. We will assess the differences between the EGE and MDR group participants (those with SCR) at baseline and before starting the treatment protocol.

For sensitivity analyses of primary and secondary, we will conduct intent-to-treat analysis (prescribed treatment), per-protocol analysis (adhered treatment) and use inverse probability weighting to determine potential outcomes had everyone adhered to their prescribed treatments.

To test the effectiveness of randomization, we will compare key variables at baseline and immediately post-injury (24-48 h timepoint) to determine differences between arms. These variables at a minimum will include: age, gender, previous history of concussion, contact/collision sport, baseline symptom severity score, 24–48 h symptom severity score. Should any differences be observed these factors will be controlled for in the models. Additionally, 24–48 h symptom severity will be considered in all analyses.

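### With 28 sites and no cohort term, the Wei-Lin robust variance used as named does not hold the primary Cox tests at the nominal 5%, in either direction

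*Protocol article*

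**What the plan says.** Under Planned Data Analysis, Specific Aim 1, the primary model is stated as follows: "Cox proportional hazards regression models (35) will be used to compare time to return to play and time to asymptomatic". The treatment of clustering is one sentence: "The Wei-Lin robust variance estimator will be used to account for the effect of cluster-randomization by site".

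Under Allocation to Study Arm, the arms "are assigned at random to the 28 sites in the study", and "site randomization is stratified by (i.e., conducted within) cohort (NZR, CFL, College, HS"). A second layer applies to schools only: "Colleges/universities and high school sites are stratified by size of school prior to randomization". Under Overview and Structure of the Active Rehab Study, the cohorts are "Canadian Football League (CFL, 9 team sites), New Zealand Super Rugby (NZR, 5 team sites), North American Colleges/Universities (6 school sites") and 8 high school sites. The expected post-injury sample is "100–200 in each study arm".

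Specific Aim 1 also says that 24-48 h symptom severity is considered throughout, and that variables from a minimum list enter the model if the arms are seen to differ on them. Cohort is not on that list.

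**The concern.** The sandwich variance for a clustered Cox model is built from one score total per site. Its justification is that the number of sites is large. Here there are 28, about 14 per arm, and the New Zealand cohort of five sites can split no more evenly than two against three. Two opposite errors are possible.

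- With few sites, the fitted score totals are smaller than the true ones, so the standard error is biased down. Uneven sites and added model terms make this worse.
- Randomisation within cohort removes between-cohort variation from the sampling error of the arm effect. A model that omits cohort still counts that variation in the site totals, so the standard error is biased up when cohorts differ.

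The net direction depends on how much cohorts differ and on whether cohort is in the model. Both primary endpoints, and any claim that MDR changes recovery time, rest on this standard error.

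**Working it through.** **The plan's own figure.** The article gives no type I error rate, alpha or sidedness, so two-sided 5% is assumed here. Its only primary-endpoint figure is 83% power at a hazard ratio of 4.5/7 with 100 per arm. Schoenfeld's formula is power = Φ(√(D/4)·|ln HR| − 1.96), with |ln(4.5/7)| = 0.442. The article also says: "We anticipate ~10–15% attrition due to study demands and seasonal nature of sport through full clearance to return to sport".

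- 10% attrition: D = 180, √45 × 0.442 − 1.96 = 1.00, power 84.2%.
- 15% attrition: D = 170, √42.5 × 0.442 − 1.96 = 0.92, power 82.1%.

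The 83% is reproduced as an individually randomised calculation. It therefore says nothing about how much variation between sites was expected.

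**Inputs from the article.** 28 sites (9, 5, 6 and 8), randomised within cohort. 200-400 athletes, so 200/28 = 7.1 to 400/28 = 14.3 per site on average. Censoring of 13%, inside the stated 10-15%.

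**Inputs assumed, because the article gives none.** Coefficient of variation (CV) of site size 0, 0.5, 0.8 or 1.0. Gamma site frailty variance 0, 0.1 or 0.3. Cohort differences: none, moderate (hazard ratio between extreme cohorts exp(0.5) = 1.65) or strong (exp(1.0) = 2.72).

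**Method.** Cox fit under no arm effect, with variance A⁻¹(Σₖ UₖUₖᵀ)A⁻¹. Uₖ is the sum of score residuals at site k and A is the information matrix. The test rejects when |estimate/SE| > 1.96. There were 2,500 runs per setting (600 for the arm + severity rows, Monte Carlo SE about 0.9 points at 5%).

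| Model | Cohort differences | Site-size CV | Type I error | Mean SE / true SD |
|---|---|---|---|---|
| Arm only | none | 0 | 6.8-8.5% | 0.81-0.95 (all four CVs) |
| Arm only | none | 0.5 | 7.0-9.1% | |
| Arm only | none | 0.8 | 7.8-11.9% | |
| Arm only | none | 1.0 | 8.2-12.1% | |
| Arm + severity, frailty 0.1 | none | 0.5-0.8 | 8.2-11.7% | |
| Arm + severity, frailty 0.1 | moderate | 0.5-0.8 | 7.2-10.8% | |
| Arm + severity, frailty 0.1 | strong | 0.5-0.8 | 3.7-5.8% | |
| Cohort left out | strong | 0-1.0 | 0.5-9.0% | 0.88-1.44 |
| Cohort terms added | | 0 | 9.1-12.2% | 0.73-0.88 (all four CVs) |
| Cohort terms added | | 0.5-0.8 | 10.0-14.2% | |
| Cohort terms added | | 1.0 | 11.8-17.0% | |
| Cohort terms + five covariates | | 0-1.0 | 9.4-17.6% | 0.70-0.87 |

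**Consistency check.** A z test whose SE is r times the true SD rejects with probability about 2Φ(−1.96r). r = 0.95 gives 6.3%, r = 0.81 gives 11.2%, r = 0.73 gives 15.2% and r = 1.44 gives 0.5%. These agree with the table. The simulated rates run a little higher at low r because the SE itself also varies from trial to trial.

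**Other assumptions, same pattern.**

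- Arm + severity, frailty variance 0.1, CV 0 or 0.6: about 8-9% with no cohort differences, 5-9% moderate and 2-6% strong with cohort left out. Stratified by cohort: 9-13%.
- Arm only, 300 athletes, CV 0, 0.5 or 0.87, with and without school-size strata: 6.6-10.7% with no differences, 3.1-8.1% moderate, 1.1-7.0% strong.

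**Corrected methods** (frailty variance 0.1, CV 0.5-0.8, 600 runs each):

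- Re-randomisation within cohort: 3.3-7.2% over 16 settings, mean 5.0%.
- Leave-one-site-out jackknife with a t reference: 4.5-6.5% for arm + severity with no cohort effects, 2.5-3.3% with cohort terms.
- A factor K/(K−1) with t on K−2 degrees of freedom, K being the number of sites: 5.4-9.6% for arm only with no cohort effects, 7.1-15.0% in adjusted models. This is not enough.

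The number of re-randomisations is not a constraint. With near-even splits in each cohort there are (2×126) × (2×10) × 20 × 70 = 7,056,000 allocations before school-size strata are applied.

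**The case against.** **Silence is not a choice.** The article is condensed and the analysis plan is not shown. It never rules out a correction or specifies a normal reference, and that detail often sits in the analysis plan. This stands as a limit: one cannot say that the analysis will be uncorrected. It does not remove the point, because the article does fix the estimator, for both primary endpoints, as the only account of clustering, and that estimator as named suits many more sites than 28. The simple correction above also fails, so which correction is used matters.

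**The direction is not fixed.** A reader might infer that the standard errors are simply too small and that the error rate of the planned test is about 8-15%. The documents do not support that. The upper part of such a range comes from models with cohort terms or strata, which Specific Aim 1 does not specify. For a model without cohort, the rate runs from about 12% down to well below 5% as cohort differences grow. The cohorts range from high school to professional sport, and the Discussion describes different providers and governing-body protocols, so equal recovery across cohorts is not a safe base case. This objection stands and shapes the conclusion.

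**The inputs are assumed.** No site-size variation or between-site variance appears in the article. Stratifying schools by size implies unequal sites but does not quantify it. This also stands. Even so, equal sites with arm only and no cohort differences give 6.8-8.5%, so some inflation there does not depend on the assumed CV.

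**Conclusion.** The point holds as one of uncontrolled error, not of uniform inflation. With a normal reference, the named estimator gives roughly:

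- 7-12% type I error if cohorts do not differ;
- less than 5%, with over-wide intervals, in many settings where cohorts differ strongly and cohort is omitted;
- 9-15% once cohort is adjusted for or stratified on, reaching 17% only with the most unequal sites or several added covariates.

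Adding cohort, the natural cure for the second case, leads to the worst inflation unless the variance is corrected too.

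These figures rest on a two-sided 5% level and on assumed site-size variation, frailty and cohort gaps. The main simulations used the four cohorts only, because the article does not give the school-size cut points. Nothing was computed for the secondary mixed models, and no claim is made about them.

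**What to change.** State four things for the two primary Cox analyses:

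1. The model is stratified by cohort, the randomisation stratum.
2. The primary p-value comes from a re-randomisation test that permutes site assignment within the strata actually used, including school size for colleges and high schools.
3. Confidence intervals use a small-sample-corrected cluster variance, for example the leave-one-site-out jackknife. The t reference has degrees of freedom reflecting sites minus strata used. With the four cohorts alone that is 28 − 4 = 24, and fewer once school-size strata are counted.
4. The p-value governs if it and the interval disagree at the margin.

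If the analysis plan already contains an equivalent correction, citing it and stating whether cohort is in the model is enough.

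The cost is a little more analysis code and somewhat wider intervals. The jackknife with cohort terms ran at about 2.5-3.3%, so those intervals may be slightly conservative. Data collection and treatment are unaffected.

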### Study Outcomes and Assessments

The primary trial endpoints include time to asymptomatic/symptom free and time to full clearance for return to sport, in days. The secondary endpoints include clinical and quality of life outcomes assessed from baseline through 1-month post return to play, as well as safety and feasibility outcomes. An assessment protocol similar to the NCAA-DOD Grand Alliance Concussion Assessment, Research, and Education (CARE) Consortium's is utilized for both baseline measurements and post-injury assessments and to achieve the primary and secondary endpoints (15). The assessment time-points for the study (Table 3) include: pre-season baseline, time of injury (optional, 24–48 h following injury, daily symptom and activity tracking through 7 days post-return to play, athlete satisfaction at 7 days post-return to play, and 1-month following full return to play. Each of the assessment timepoints are collected at the approximate windows, i.e., within 5 days, due to the nature of athletic schedules. Study measures are administered by trained site personnel and clinicians. Assessments take place at site medical and training facilities. Below are brief descriptions of all study measures.

**Table 3 T3:** Assessment schedule.

	**Demographics**	**Personal and family history**	**SCAT symptom checklist**	**QOL**	**BSI-18**	**Neurocognitive assessment**	**SAC**	**BESS**	**NPC**	**Dual-task**	**Start and end fatigue rating**
**Pre-season baseline**	✓	✓	✓	✓	✓	✓	✓	✓	✓	✓	✓
**Time of injury (within 6 h—if possible)**			✓				✓	✓			
**24–48 h post-injury**			✓		✓	✓	✓	✓	✓	✓	✓
**Asymptomatic post-injury**			✓	✓	✓	✓	✓	✓	✓	✓	✓
**1-month post return to play post-injury**			✓	✓	✓	✓	✓	✓	✓	✓	✓
- Symptoms and activity assessed daily from the first assessment point until 7 days post return to play - Concussion Index completed following injury - Recovery Form completed following return to play - *Participant Satisfaction completed at 7-days post return to play*											

*QOL, Quality of Life; BSI-18, Brief Symptom Inventory 18 item; SAC, Standardized Assessment of Concussion; NPC, Near Point of Convergence; SCAT, Sport Concussion Assessment Tool*.

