**Brief Symptom Inventory-18 (BSI-18):** Psychological distress is measured utilizing the BSI-18. The BSI-18 is a brief symptom inventory with high reliability (21). The assessment gathers athlete-reported data to help measure psychological distress in primary care settings (21). Participants rate their level of distress associated with 18 symptom items on a scale from 0 (not at all) to 4 (extreme). Ratings are then added together to compute an overall symptom distress score. *Time points collected: Baseline, 24–48 h Post-Injury, Asymptomatic Post-Injury, and 1-month post return to play*.

**Health-Related Quality of Life (HRQL**): Participants' HRQL is assessed using the Athlete-Reported Outcomes Measurement Information System (PROMIS-29), and the Quality of Life in Neurological Disorders (Neuro-QOL) Cognition and Fatigue Scales. These scales have high reliability and validity concerning overall quality of life (22–24). Outcomes will include the PROMIS-29 and Neuro-QOL summary scores (anxiety, physical function, depression, sleep disturbance, social role/activities, pain interference, pain intensity, Neuro-QOL cognition, and Neuro-QOL fatigue). These scales ask the participant to rate items on a Likert type scale ranging from 1 to 5 (higher or lower score indicating “worse” is dependent upon the item). *Time points collected: Baseline, Asymptomatic, 1-month post return to play*.

**Computerized Neurocognitive Testing**: Participant neurocognitive performance at baseline and post-injury will be assessed utilizing the computerized neurocognitive testing platform currently used clinically at each site. The platforms to be included by study sites include Immediate Postconcussion Assessment and Cognitive Test (ImPACT), CogSport, and Concussion Vital Signs. Reliability and validity of computerized tests varies and has been established in previous literature (25, 26). Each platform includes alternating forms and presentation variation. *Time points collected*: *Baseline, 24–48 h post injury, Asymptomatic, and 1-month post return to play*.

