**Figure 6 F6:**
[figure not shown]
Balance Error Scoring System (BESS) stances. Written informed consent was provided by the individual in the image for publication. **(A)** Double leg firm, **(B)** single leg firm, **(C)** tandem stance firm, **(C)** double leg foam, **(E)** single leg foam, and **(F)** tandem stance foam (29).

**Near Point Convergence**: The Near Point of Convergence (NPC) test will function as the visual/oculomotor exam for this study (31). NPC is measured by drawing a tongue depressor with a dot in 14-point font from arm's length toward the participant's nose. The participant is instructed to stop the approximation at the point the visual target is seen in double (diplopia). The clinician then measures the distance between the tip of the nose and the tongue depressor in centimeters. Three trials are collected and averaged. NPC has been shown to be a reliable measure (32). *Time points collected: Baseline, 24–48 h post injury, Asymptomatic, and 1-month post return to play*.

**Dual-task**: Dual-task performance will be assessed via the Walking and Remembering Dual-Task Assessment (ISAW-Grid Task) (33) which has been previously reported as potentially useful for physically active individuals (34) and evaluates divided attention cost across a gait and cognitive task. Participants walk 3.5 m toward a target and then turn and walk back to the start line and the walk time is recorded. Participants are then given 2 numbers and 6 letters from the military phonetic alphabet and asked to recall the information accurately and in order. Alternate word list are given at each time point. Following these single tasks, the individual is then asked to combine the task. The examiner gives the individuals 2 numbers and 6 letters to remember, the participant completes the gait task, and upon return to the start line, the participant is asked to recall the numbers and letters (Figure 7). Gait time and accuracy are scored and coded as the initial outcomes. Performance in the dual-task is then compared for each of these outcomes to the single task, yielding the primary outcome of dual-task cost. Participants will be asked to complete a cognitive (immediate recall) task while also completing a walking task of 7 m. *Time points collected: 24–48 h post injury, Asymptomatic, and 1-month post return to play*.

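### Each secondary mixed model should adjust for the measure's own pre-season value as a fixed rule, not only when the arms are seen to differ

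*Protocol article*

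**What the plan says.** All references are to the protocol article.

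- **Secondary model** (Planned Data Analysis, Specific Aim 1): "recovery trajectories will be examined by use of General Linear Mixed regression models and non-parametric smoothers". On the error structure: "Random effects will be utilized to account for the effect of clustering by site and the effect of repeated observations over time within an individual". Time is continuous, and the axis is described thus: "The time axis to be modeled in both sets of analyses is time from initiation of the treatment (defined as stable symptoms for 24 h".
- **Adjustment rule** (same section): key variables are compared between arms at baseline and at 24–48 h. The list, given as a minimum, is "age, gender, previous history of concussion, contact/collision sport, baseline symptom severity score, 24–48 h symptom severity score". Then: "Should any differences be observed these factors will be controlled for in the models". The one factor to be considered in every analysis is 24–48 h symptom severity.
- **Data collected** (Study Outcomes and Assessments): "The secondary endpoints include clinical and quality of life outcomes assessed from baseline through 1-month post return to play". Table 3 ticks the symptom checklist, quality of life, BSI-18, neurocognition, SAC, BESS, NPC and dual-task at pre-season.
- **Quality of life** (measure description): "Time points collected: Baseline, Asymptomatic, 1-month post return to play". There is no 24–48 h assessment.
- **Dual-task** (measure description): "Time points collected: 24–48 h post injury, Asymptomatic, and 1-month post return to play". Pre-season is not listed here, but Table 3 ticks it.

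**The concern.** An athlete's own pre-season score is usually the strongest available predictor of the same score after injury. The plan collects it but secures its use only through a rule of comparing first and adjusting second, and that rule names the pre-season value of one measure. The value of a prognostic covariate lies in its correlation with the outcome, not in whether the arms happen to differ on it. A rule triggered by observed imbalance therefore discards precision whenever the arms look alike, and it makes the final model depend on the data.

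At stake is the standard error of any comparison of post-injury level between arms. Arm is constant within athlete and within site, so variation between athletes enters that standard error in full. Quality of life is the clearest case. Its two post-injury visits, asymptomatic and 1 month after return to play, normally both come after treatment starts. A benefit already present at the first of them shows as a difference in level rather than in slope. The pre-season value is then the only measurement taken before treatment.

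**Working it through.** **The plan's own figure.** The article gives no power figure for the secondary models. Its only figure, 83% power for time to asymptomatic with 100 per arm and a hazard ratio of 4.5/7, reproduces. Under Freedman's formula with 10% attrition (180 events) and two-sided 5% (assumed), √180 × 2.5/11.5 − 1.96 = 0.957, which gives 83.1%. It does not bear on this point.

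**Inputs**
- 100 per arm (Sample size) and 20–30% attrition at 1 month (Participants and Eligibility Criteria). The midpoint leaves 100 × 0.75 = 75 per arm.
- Correlation ρ between pre-season and post-injury values: not in the documents. Assumed 0.5, range 0.3–0.7.
- Arm difference of 0.4 SD and two-sided 5%: assumed.
- No intracluster correlation is given, so the main calculation ignores clustering.

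**1. Level at one time point.** SE = √(2/n × (1 − ρ²)). Power = Φ(0.4/SE − 1.96). Detectable difference at 80% power = (1.96 + 0.842) × SE. With n = 75:

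| ρ | Variance factor 1 − ρ² | SE reduction | Power at 0.4 SD | Detectable difference (SD) |
|---|---|---|---|---|
| unadjusted | 1 | – | 68.8% | 0.457 |
| 0.3 | 0.91 | 4.6% | 72.8% | 0.436 |
| 0.5 | 0.75 | 13.4% | 80.7% | 0.396 |
| 0.7 | 0.51 | 28.6% | 92.9% | 0.327 |

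Example at ρ = 0.5: SE = √(0.02667 × 0.75) = 0.1414; 0.4/0.1414 − 1.96 = 0.868; Φ = 80.7%. Across the stated attrition range (80 to 70 per arm), the detectable difference goes from 0.443–0.474 unadjusted to 0.384–0.410 at ρ = 0.5. With an assumed design effect of 1.09, power goes from 65.0% to 77.3% at ρ = 0.5, so the gain is similar.

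**2. Mean of two post-injury visits** (the quality-of-life pattern, equal correlations). The variance goes from (1 + ρ)/2 to (1 + ρ)/2 − ρ². That is 0.65 to 0.56 at ρ = 0.3 (14% less), 0.75 to 0.50 at 0.5 (33% less) and 0.85 to 0.36 at 0.7 (58% less).

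**3. Repeated-measures model.** A simulation of a random-intercept model (2,000 replicates, 100 per arm, days 0, 7 and 37, equal correlations, no site effect, no true arm effect) gave these standard errors:

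| ρ | Level at day 37: unadjusted → adjusted | Slope contrast: unadjusted → adjusted |
|---|---|---|
| 0.3 | 0.141 → 0.135 | 0.160 → 0.160 |
| 0.5 | 0.143 → 0.124 | 0.136 → 0.136 |
| 0.7 | 0.138 → 0.100 | 0.103 → 0.103 |

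The average estimates stayed within 0.007 of zero with and without adjustment. The gain is therefore confined to level. A covariate that does not change over time carries no information on the slope contrast in this model.

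**4. Dual-task.** The measure description lists three post-injury time points, and Table 3 ticks those three plus pre-season. Both cannot be right.

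**The case against.** **The full covariate list may sit in an analysis plan that is not shown.** This is fair against any claim of bare omission. The article is not merely silent, however. It commits to adjustment conditional on an observed difference, and that stated rule is what needs changing.

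**A reader might infer that the pre-season values go entirely unused, or that starting the clock at treatment shuts them out.** The documents do not support either. The list of compared variables is a minimum, and pre-season symptom severity is adjusted for if the arms differ on it. A pre-season covariate can be used with any time zero. The time axis matters only if the pre-season value were fitted as a point on the continuous trend.

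**A reader might infer that the plan confuses recovery with stable differences between athletes, or that its arm comparison is biased.** It does not follow. The participant random effect separates stable differences from change over time. Randomization keeps the unadjusted contrast unbiased in expectation. Stratification by cohort, and by school size for colleges and high schools, removes much of the gap between high-school and professional athletes. Chance differences between the 28 sites remain, but they widen the standard error and are not bias. Entry after injury, by clinicians who know the arm, is a separate matter on which this point does not rest.

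**The stated target is trajectories, and the size rests on assumptions.** Both stand in part. If only the slope contrast is reported, little or nothing is gained. At a correlation of 0.3 the power gain is about 4 points. Measures with a 24–48 h value have another early measurement and may gain less than quality of life.

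**Conclusion.** The point holds as a question of precision. The plan makes adjustment for pre-season values conditional on an observed arm difference and names only one such outcome score, although it collects all of them. For arm differences in post-injury level, the avoidable variance is about 9–49% for an assumed correlation of 0.3–0.7. At 0.5, with 75 per arm and an assumed 0.4 SD difference, power is 69% instead of 81%. The consequence is greatest for quality of life.

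The correlation, the effect size and the absence of clustering in the main calculation are assumptions. The finding concerns neither bias nor slope contrasts, and it does not affect the primary endpoints or their sample size. The dual-task discrepancy needs no assumption. If sites follow the measure description, that baseline is lost and cannot be recovered after injury.

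**What to change.** In Planned Data Analysis, Specific Aim 1, state that every secondary mixed model includes the athlete's own pre-season value of that measure as a fixed covariate, whether or not the arms differ on it. State also that the pre-season value is not fitted as a point on the continuous time trend that starts at treatment. Keeping it in the outcome vector with a separate baseline term is an acceptable alternative.

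In Study Outcomes and Assessments, reconcile the dual-task time points with Table 3 so that sites know whether the pre-season test is due.

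The cost is one sentence, one correction and no new data. The small downside is that athletes with a missing pre-season value on a measure need a stated handling rule, such as simple covariate imputation.
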